#### 10.4.2 SERIOUS ADVERSE EVENT REPORTING

The PI/SI will complete a SAE Form within the following time frame:

- All SAEs will be recorded on the SAE Form and submitted by the site PI to the Overall study PI/Sponsor within 24 hours of initial receipt of the information (weekends and holidays are not included) and addressed to:
- [name] [name]  
Study Medical Monitor  
International Vaccine Institute  
[name]  
[contact]-XXXX (Dir)  
[contact]  
E-mail: [[contact]](mailto:[contact])

- NHRC to be notified within 2 calendar days by the sponsor/overall study PI/Designee with complete report due within 21 additional calendar days of the first information.

All information (which may include special investigations and treatment received) will be recorded on the SAE Form and submitted to the NRA and site-specific IRB/IEC. All SAEs will be followed until satisfactory resolution or until the site investigator deems the event to be chronic or to be stable. Other supporting documentation of the event may be requested by the sponsor and should be provided as soon as possible. SAE reporting to IVI IRB on regular basis is not mandatory (except those are of SUSAR category) and will be reported with the annual renewal report.

- The sponsor will be responsible for notifying the IVI IRB of Suspected Unexpected Serious Adverse Reactions (SUSAR) within 24 hours of initial receipt of the information (weekends and holidays are not included)

The SUSAR report will include the following information:

- Protocol information: protocol number and date
- A detailed description of the event, incident, experience, or outcome
- An explanation of the basis for determining that the event, incident, experience, or outcome represents an unexpected problem

---

#### 10.4.3 SAFETY OVERSIGHT

An internal **Safety Monitoring Committee (SMC)** will be responsible to oversee the vaccine safety patterns during the clinical trial. The SMC will be composed of individuals with appropriate expertise. The SMC will review blinded safety data on a regular basis according to the guidelines of the SMC charter. The SMC will send a summary of safety review findings to the site PIs, DSMB members, and the Study Medical Monitor.

An independent **Data Safety Monitoring Board (DSMB)** will be constituted of experts from various fields of Medicine external to sponsor's organization. The DSMB will oversee the study in terms of safety data as per DSMB charter. DSMB chair will issue a recommendation letter after each meeting. The DSMB will provide independent recommendations to the Sponsor and subsequently to Principal Investigator. The decision on whether to resume the study will be taken by the Sponsor and the Principal Investigator, based upon the recommendations of the DSMB.

The decision taken will then be communicated to the IRB/IEC and National Regulatory Agencies along with the DSMB recommendation by the principal investigators.

## 11. STUDY MONITORING

Before the inclusion of the first participant in the center, the Investigators and the Sponsor's monitoring staff, or a representative will meet at the site-initiation visit to discuss the trial protocol and the detailed trial procedures. Emphasis will be placed on inclusion and exclusion criteria, visit timing, safety procedures, informed consent procedures, SAE reporting procedures, eCRF completion, and the handling of samples and products.

Study monitoring and auditing will be performed in accordance with the sponsor's procedures, ICH E6 (R2) GCP guidelines and any other applicable regulatory requirements.

Upon successful approval of the protocol and establishment of the Regulatory File, the clinical monitor will establish a clinical monitoring plan (CMP). To ensure that the investigator and the study staff understand and accept their defined responsibilities, the clinical monitor will maintain regular correspondence with the site and may be present during the course of the study to verify the acceptability of the facilities, compliance with the investigational plan and relevant regulations, and the maintenance of complete records.

Investigators and/or their study staff will be trained on the study protocol and all applicable study procedures prior to study initiation. Electronic CRFs supplied by the sponsor must be completed for each enrolled participant. The data entries as well as study related documents will be checked by the sponsor and/or trained delegates of the sponsor.

Study progress will be monitored by IVI study team or representative (e.g., a clinical research organization) as frequently as necessary to ensure the rights and well-being of study participants are protected; to verify adequate, accurate and complete data collection; protocol compliance and to determine that the study is being conducted in conformance with applicable regulatory requirements. Arrangements for monitoring visits will be made in advance in accordance with the monitoring plan, except in case of emergency.

A report of monitoring observations will be provided to the principal investigator. All clinical and research records must be available for review by the sponsor's representative, local IRB

representatives, and other regulatory agencies as part of their responsibilities for insuring the protection of research participants.

At the end of the trial, a close-out visit will be performed to ensure that:

- The center has all the documents necessary for archiving
- All samples have been shipped to the appropriate laboratories
- All unused materials and products have been either destroyed or returned to the Sponsor

## 12. QUALITY ASSURANCE AND QUALITY CONTROL

Quality Assurance (QA) oversight will be required at all stages of the trial process per ICH E6 (R2) and/or local government GCP requirements.

Quality Control (QC) procedures will be implemented beginning with the data entry system and data QC checks. Any missing data or data anomalies will be communicated to the site(s) for clarification/resolution.

During study conduct, the sponsor or its designee (e.g., CRO) will conduct periodic monitoring visits (*i.e.*, QC checks) to ensure that the protocol, Good Clinical Practice, local regulatory requirements and sponsor's controlled documents (e.g., Standard Operating Procedure) are being followed. The monitors will review source documents to confirm that the data recorded on CRFs/eCRFs are accurate.

In addition to on-going QA oversight, selected investigator sites will be subjected to quality assurance audits performed by the sponsor or its designee, and/or by inspection by regulatory authorities and/or notified bodies.

The investigational sites will provide direct access to all study related sites, source data/documents, and reports for the purpose of monitoring and auditing by the sponsor; inspection by local and regulatory authorities and/or notified bodies.

## 13. STATISTICAL CONSIDERATIONS

### 13.1 STUDY ENDPOINTS

#### 13.1.1 PRIMARY IMMUNOGENICITY ENDPOINT

- Proportion of participants showing seroconversion of vibriocidal titers against *Vibrio cholerae* O1 Inaba and O1 Ogawa (seroconversion is defined as at least 4-fold increase of vibriocidal titers against *V. cholerae* O1 Inaba and O1 Ogawa compared to baseline) at 2 weeks after second dose of either OCV-S (*i.e.*, one lot of OCV-S) or Shanchol™ for all ages.

#### 13.1.2 PRIMARY SAFETY ENDPOINT

- Frequency of solicited adverse events within 7 days post vaccination, unsolicited adverse events within 28 days post vaccination, and SAEs after each dose during the entire study period in all ages and in each age stratum.

#### 13.1.3 SECONDARY ENDPOINTS

- Geometric Mean Titer of vibriocidal antibodies against *Vibrio cholerae* O1 Inaba and Ogawa 2 weeks after second dose of either OCV-S (*i.e.*, one lot of OCV-S) or Shanchol™ for all ages
- Proportion of participants showing seroconversion against *Vibrio cholerae* O1 Inaba and Ogawa 2 weeks after second dose of either OCV-S (*i.e.*, one lot of OCV-S) or Shanchol™ in each age stratum
- Geometric Mean Titer of vibriocidal antibodies against *Vibrio cholerae* O1 Inaba and Ogawa 2 weeks after second dose of either OCV-S (*i.e.*, one lot of OCV-S) or Shanchol™ in each age stratum
- Geometric Mean Titer of vibriocidal antibodies against *Vibrio cholerae* O1 Inaba and Ogawa 2 weeks after second dose of 3 lots of OCV-S in adults

#### 13.1.4 EXPLORATORY ENDPOINT

- Proportion of participants showing seroconversion of vibriocidal titers against *Vibrio cholerae* O1 Inaba and Ogawa 2 weeks after second dose of 3 lots of OCV-S in adults
- Seroconversion rate and GMT of vibriocidal antibodies 2 weeks after first dose of either OCV-S or Shanchol™ for all ages and for each age stratum

## 13.2 SAMPLE SIZE

The sample size of the study is calculated to provide about 90% power to show primary Immunogenicity objective of immune non-inferiority of OCV-S to Shanchol™ and secondary immunogenicity objective of immune equivalence of three lots of OCV-S of the study and increased to satisfy total safety population of about N=2,530. The given sample size of N=935 participants per OCV-S and Comparator vaccine group in all ages would provide 99% power to detect the non-inferiority of immunogenicity of OCV-S group (Group C) compared to Shanchol™ (Group D) in terms of seroconversion rate. The assumed seroconversion rate of Shanchol™ is 71% for all ages which is considered in the assumption based on the clinical studies conducted in a neighboring country to Nepal (i.e., India). The sample size of N=330, 360, and 245 participants per OCV-S and Shanchol™ would provide 80% power to detect non-inferiority of OCV-S in terms of seroconversion rates of 75%, 71%, and 84% in adults, adolescents, and young children, respectively. The assumed non-inferiority margin is -10% based on WHO TRS 924. One sided test of non-inferiority is used with significance level of 0.025.

The sample size of N=330 per lot of OCV-S in adults will also provide >90% power for three equivalence tests of GMT ratio of immunogenicity among three lots of OCV-S (A vs. B, B vs. C and C vs. A) with overall two-sided significance level of 0.05. Each of two-sided equivalence test have >90% power to show the equivalence of GMT of immunogenicity of OCV-S with two-sided significance level of 0.05. The equivalence margin of ratio was assumed as [0.5, 2.0] according to precedent study of OCV (i.e., Euvichol®) and other oral vaccine trials, the true GMT ratio is assumed as 1 and the coefficient of variation on titer of immunogenicity is assumed as 2.0. The coefficient of variation of GMT of OCV-S was assumed conservatively based on OCV immunogenicity data. In both sample size calculations, 10% drop out rate is assumed conservatively considering the potential large variation of experience between sites.

## 13.3 STATISTICAL ANALYSIS PLAN

The statistical analysis will focus on comparisons of immunogenicity of OCV-S (Group C) and Shanchol™ (Group D), and on tests of lot consistency of OCV-S (pair-wise comparison of Group A, B and C in adults) at 2 weeks post second dose of vaccination. Safety of OCV-S will be assessed by descriptively comparing incidence of common solicited, unsolicited and serious AE between OCV-S and Shanchol™ and any incidence of unexpected AE. The statistical analysis will be performed when all participants complete the Day 182 visit (24 weeks post second dose). Immunogenicity and safety data up to Day 182 will be included in the analysis.

#### 13.4 STATISTICAL HYPOTHESES

The primary comparison to show the non-inferiority of OCV-S compared to Shanchol™ is

- Seroconversion rate of vibriocidal titers against *Vibrio cholerae* O1 Inaba and O1 Ogawa at 2 weeks after second dose of OCV-S (Group C) is non-inferior to seroconversion rate at 2 weeks after second dose of Shanchol™ (Group D) using noninferiority margin of -10%

The secondary comparison to demonstrate the lot consistency of OCV-S is

- Geometric Mean Titer of vibriocidal antibodies against *Vibrio cholerae* O1 Inaba and O1 Ogawa at 2 weeks after second dose of each lot of OCV-S is equivalent to each other (A vs. B, B vs. C, and C vs. A) using equivalence margin of GMT ratio of [0.5, 2.0]

No multiplicity adjustment of primary and secondary comparison. The non-inferiority test of OCV-S vs. Shanchol™ will be performed using one sided significance level of 0.025 and three equivalent tests will be performed using two-sided significance level of 0.05.

Following secondary comparisons are tested using the one-sided significance level of 0.025 for non-inferiority.

- GMT of vibriocidal antibodies against *Vibrio cholerae* O1 Inaba and Ogawa at 2 weeks after second dose of OCV-S (Group C) is non-inferior to GMT at 2 weeks after second dose of Shanchol™ (Group D) using non-inferiority margin of GMT ratio of 0.67
- Seroconversion rate of vibriocidal titers against *Vibrio cholerae* O1 Inaba and O1 Ogawa at 2 weeks after second dose of OCV-S (Group C) is non-inferior to seroconversion rate at 2 weeks after second dose of Shanchol™ (Group D) using noninferiority margin of -10% in each age stratum

- GMT of vibriocidal antibodies against *Vibrio cholerae* O1 Inaba and Ogawa at 2 weeks after second dose of OCV-S (Group C) is non-inferior to GMT at 2 weeks after second dose of Shanchol™ (Group D) using non-inferiority margin of GMT ratio of 0.67 in each age stratum

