### 4.2 SECONDARY OBJECTIVES

- To demonstrate non-inferiority of OCV-S compared to Shanchol™ as measured by GMT of vibriocidal titers against *V. cholerae* O1 Inaba and *V. cholerae* O1 Ogawa 2 weeks after second dose (*i.e.*, one lot of OCV-S) for all ages
- To demonstrate non-inferiority of OCV-S compared to Shanchol™ as measured by seroconversion rates of vibriocidal titers against *V. cholerae* O1 Inaba and *V. cholerae* O1 Ogawa 2 weeks after second dose (*i.e.*, one lot of OCV-S) in each age stratum
- To demonstrate non-inferiority of OCV-S compared to Shanchol™ as measured by GMT of vibriocidal titers against *V. cholerae* O1 Inaba and *V. cholerae* O1 Ogawa at 2 weeks after second dose (*i.e.*, one lot of OCV-S) in each age stratum
- To demonstrate the equivalence of immunogenicity as measured by GMT of vibriocidal titers against *V. cholerae* O1 Inaba and *V. cholerae* O1 Ogawa of 3 lots of OCV-S 2 weeks after second dose in adults

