#### 13.6.5 SECONDARY ENDPOINTS ANALYSIS

GMT of vibriocidal antibodies against *Vibrio cholerae* O1 Inaba and O1 Ogawa at 2 weeks post second dose will be calculated by vaccine group and for all ages and by age strata. The two-sided 95% CI of GMT and ratio of GMTs will be provided. The non-inferiority of OCV-S will be confirmed if the lower limit of two-tailed 95% CI of the ratio of GMT of OCV-S (Group C) to Shanchol™ (Group D) is greater than the non-inferiority margin of 0.67.

Seroconversion rate of vibriocidal antibodies against *Vibrio cholerae* O1 Inaba and O1 Ogawa at 2 weeks post second dose will be calculated by vaccine group by age strata. The two-sided 95% CI of seroconversion rate and difference of seroconversion rates will be provided. The non-inferiority of OCV-S will be confirmed if the lower limit of the two-sided 95% CI of the difference of seroconversion rate of OCV-S (Group C) and Shanchol™ (Group D) is greater than the pre-defined non-inferiority margin of -10%.

To assess lot consistency, three equivalence tests (Group A vs B, A vs C, B vs C) on GMT of vibriocidal antibody responses against *Vibrio cholerae* O1 Inaba and O1 Ogawa at 2 weeks after second dose of 3 lots of OCV-S will be performed with two-sided significance level of 0.05. The equivalence of GMT at 2 weeks after second dose of two lots of OCV-S will be analyzed using the analysis of variance (or covariance if necessary) model after log transformation. The equivalence of two lots will be confirmed if both limits of the two-sided 95% confidence interval of the ratio of the GMT between two lots of OCV-S is within the equivalence margin of [0.5, 2.0].

Secondary immunogenicity endpoints analysis will be conducted on the participants in the PPS and FAS.

---

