#### 13.6.9 MULTIPLE COMPARISON/MULTIPLICITY

No multiplicity adjustment is taken relative to non-inferiority and lot consistency tests.

---

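### Seven secondary non-inferiority claims and the lot claim are each tested at full alpha with no order or gate, so the familywise error behind results worded as demonstrated can reach about 11-15% in the worst case (13-17% with lots), and more if each serotype is claimed separately

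*Protocol*

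**What the plan says.** Section 13.4 gives one primary immunogenicity comparison: all-ages seroconversion, Group C against Group D, margin -10%. On the rest it says "No multiplicity adjustment of primary and secondary comparison", and for lot consistency "three equivalent tests will be performed using two-sided significance level of 0.05". It continues: "Following secondary comparisons are tested using the one-sided significance level of 0.025 for non-inferiority". The comparisons listed there are all-ages GMT (ratio margin 0.67), seroconversion in each age stratum (margin -10%) and GMT in each age stratum (margin 0.67). Section 13.6.9 repeats the rule: "No multiplicity adjustment is taken relative to non-inferiority and lot consistency tests".

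Section 4.2 gives these comparisons confirmatory wording. The stratum objective, for example, opens "To demonstrate non-inferiority of OCV-S compared to Shanchol™ as measured by seroconversion rates of vibriocidal titers against" the two serotypes, and the other three secondary objectives use the same verb. Section 13.6.5 attaches a decision rule to each, for example "The non-inferiority of OCV-S will be confirmed if the lower limit of two-tailed 95% CI of the ratio of GMT" exceeds 0.67, and for lots "The equivalence of two lots will be confirmed if both limits of the two-sided 95% confidence interval of the ratio of the GMT" lie inside [0.5, 2.0].

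Two other places bear on the status of the stratum results. Section 13.2 sizes each stratum for 80% power. Section 13.6.8 lists the immunogenicity analyses by age stratum under additional sub-group analysis.

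**The concern.** The protocol separates objectives it will demonstrate (4.1, 4.2) from those it will only describe (4.3, and stratum-level safety in 4.1). A reader will therefore take a secondary success as a confirmatory finding. Nothing in the document limits how often at least one such finding is false, and nothing ties them to the primary: a stratum could meet its rule in 13.6.5 and be reported as confirmed although the all-ages comparison had failed.

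This is not a detail left for the statistical analysis plan. The protocol addresses multiplicity in two sections and rules adjustment out in both. It also leaves the status of the strata unsettled, because 4.2 and 13.2 treat them as confirmatory while 13.6.8 lists them as sub-group analyses.

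**Working it through.** **Count of claims (13.4).** All-ages GMT 1 + stratum seroconversion 3 + stratum GMT 3 = 7 non-inferiority claims. Each names two serotypes, so there are 7 × 2 = 14 tests. Lot equivalence is one further claim. Because all its pairs must pass, it needs no adjustment within itself and adds at most 2.5%.

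**The plan's own power figures (13.2).** Inputs: one-sided 0.025, margin 0.10, equal true rates, 10% dropout. Power = Φ(0.10 / √(2p(1−p)/n) − 1.96), for one serotype.

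| Comparison | p | n per arm after dropout | Power | Stated |
|---|---|---|---|---|
| All ages | 0.71 | 841 | 99.5% | 99% |
| 18-40 years | 0.75 | 297 | 80.4% | 80% |
| 6-17 years | 0.71 | 324 | 80.1% | 80% |
| 1-5 years | 0.84 | 220 | 81.6% | 80% |

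These reproduce. For lots, log SD = √ln(1 + 2.0²) = 1.27 and n = 297, which gives above 99.9% against the stated >90%. Each stratum test was therefore sized at the full 0.025 and for a single serotype.

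**Familywise error, without assumed correlations.** The strata contain different participants, so their tests are independent. Three seroconversion tests at the margin give 1 − 0.975³ = 7.3%, which is 2.9 times the per-test level. If a claim needs both serotypes, this is the case where one serotype is at its margin and the other is clearly non-inferior. Treating all tests as independent gives the reference values 1 − 0.975⁷ = 16.2% and 1 − 0.975¹⁴ = 29.8%.

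**Familywise error, with correlations.** Simulation used 400,000 runs, three independent strata, and the all-ages GMT statistic built as the size-weighted sum of the strata (330:360:245). Every null was set at its margin. Correlations between serotypes, and between seroconversion and GMT, were varied from 0 to 0.9; the protocol gives none, so these are assumptions.

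| Definition of a claim | Seven claims | With lots |
|---|---|---|
| Both serotypes must pass; one at margin, the other clearly non-inferior (worst case) | 11-15% | 13-17% |
| Both must pass, both at margin | 0.4-9% | not computed |
| Each serotype its own claim (14 tests) | 15-28% | 17-30% |

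**Milder states.** If one stratum is at its margin on both seroconversion and GMT (one serotype, correlation 0.8 to 0.3), the rate is 3.9-4.8%. With two such strata it is 7.7-9.3%.

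**Power under an ordered plan.**
- All-ages GMT: the SE of the log ratio is 1.27 × √(2/841) = 0.062 and ln(0.67) = −0.40, so power is above 99.9%. This borrows the CV of 2.0 and true ratio of 1, which 13.2 gives only for lots in adults.
- Holm, first step at 0.025/3: stratum seroconversion power is 66.3%, 65.9% and 68.0% per serotype.
- Bonferroni over seven claims (0.00357), for comparison: about 55%, 55% and 57%.

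**The case against.** The strongest reply is that the large figures describe an extreme state. If all three strata sit at -10 points, the all-ages difference does too. The primary is then also truly null and fails at least 97.5% of the time, so a false secondary claim alongside a successful primary has probability of at most 2.5%. This is correct. It means the figures are maxima, and it is an argument for writing in the gate, because as the protocol stands a false stratum claim counts whether or not the primary succeeds. A gate alone is not enough, however: with one or two strata at the margin the primary may succeed, and the rates are still about 4-5% and 8-9%.

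The protocol is also open about its choice. A reader might infer that it promises 2.5% for the secondary family and breaks that promise. It does not: 0.025 is a level per test, and the absence of adjustment is declared.

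Four other stronger readings should be set aside.
- A single error rate near 25% for the seven claims needs each serotype to be a separate claim. The objectives name Inaba and Ogawa together, so requiring both is the natural reading, although the protocol does not say so for the secondary claims.
- The primary error rate is not inflated. There is one primary immunogenicity comparison, held at 2.5% if both serotypes must pass.
- The three lot pairs do not inflate error among themselves.
- No section says the stratum claims are what supports use in ages 1-5 or 6-17. Section 15.3 says only that all data support licensure and prequalification.

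Finally, 13.6.8 lets a reader treat the strata as ordinary sub-group analyses. That is a fair reading of that section, but it conflicts with the wording of 4.2 and the stratum sizing in 13.2, so it shows an unsettled status and does not answer the point.

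**Conclusion.** The point holds as a weakness in the secondary claims only. Seven non-inferiority claims and a lot claim carry confirmatory wording and decision rules at full alpha, with adjustment ruled out and no dependence on the primary. Under the natural both-serotype reading, the familywise error can reach about 11-15% (13-17% with lots); if serotypes are claimed separately, about 15-30%. These are worst cases, with every comparison at its margin and correlations assumed, and not the expected chance of a false claim. The firmest single figure is 7.3% for the three seroconversion strata, which needs no assumed correlation. The amendment is worth making because it is cheap.

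**What to change.** Replace the no-adjustment sentences in 13.4 and 13.6.9 with the following, and align 4.2 and 13.6.5:

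1. No secondary claim is confirmatory unless the primary all-ages seroconversion comparison succeeds.
2. Next, test all-ages GMT non-inferiority at one-sided 0.025.
3. If step 2 succeeds, test lot-to-lot GMT equivalence, all three pairs, under the existing confidence interval rule.
4. Report seroconversion and GMT by age stratum as supportive estimates with 95% CIs, with 4.2 reworded to estimate. These do not depend on the lot result.
5. State whether a claim requires both serotypes. With both required, the sequence holds the familywise error at 2.5% or less.

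If confirmatory stratum claims are wanted, insert stratum seroconversion between steps 2 and 3 with Holm across the three strata. Lots should not come before the strata. Lot equivalence is assessed in adults only, and 7.1.1 explains that one lot was used for the primary so that a failing consistency lot would not sink it; gating child strata on lots would work against that reasoning.

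**Cost.** Wording only; sample size and the primary test are unchanged. Later claims are lost when an earlier step fails, which is unlikely in the main sequence: power is 99.5% for the primary, above 99.9% for lots, and above 99.9% for all-ages GMT if the lot CV is borrowed. The strata lose their confirmatory label. The Holm option lowers first-step power per stratum and serotype from about 80% to 66-68%. It also means that, if lots are tested only after all three strata succeed, they are reached at most 0.8035 × 0.8009 × 0.8162 = 52.5% of the time per serotype. The sponsor should weigh that before choosing it.
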